#### Treatment Allocation

It is not possible to blind local investigators to allocation as it is obvious clinically which patients are receiving hypothermia e.g. equipment required, patient temperature, blood results, fluid requirements. Blinding of outcome data assessment is however be ensured as the GOSE questionnaire is posted to participants by the coordinating centre.

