#### Follow-up Data

The patient's General Practitioner/Family Doctor is sent a letter by post to inform them of the patient's involvement in the Eurotherm3235Trial.

Patient outcome is assessed 6 months after injury using the GOSE questionnaire. As this is the primary endpoint of the study, it is vital that this information is obtained. If the patient is still in hospital 6 months after the injury, the research nurse or investigator may visit the patient on the ward to go through the questionnaire with them if this is appropriate. If however the patient has been discharged from hospital, the questionnaire is sent to their residing address. A member of the trial team will telephone the patient's family doctor to find out their vital status before any questionnaires are sent to the patient.

It is likely that the patient is unable to complete the questionnaire by themselves due to the nature of their injury. Therefore a letter will also be sent to the person who gave consent for the patient inviting them to help the patient to complete the form and remind them of the study. This is sent at the same time as the GOSE questionnaire is sent to the patient. If a response is not received from the patient within 3 weeks, they are sent the shorter GOS questionnaire with a covering letter.

If there is still no response, and the patient has been discharged from hospital, an attempt will be made to contact them directly by telephone. If the patient lacked capacity at hospital discharge and cannot be contacted directly by telephone, the person who consented for the patient to be enrolled in the study is telephoned and asked to complete the shorter GOS questionnaire over the telephone.

If however the patient regained capacity before hospital discharge and has given consent to continue to be involved in the follow-up phase of the study, yet cannot be contacted directly by telephone, no further contact is made. This process is discussed during the consent procedure.

Staff in Edinburgh work closely with local investigators to obtain data that are as complete and accurate as possible. Key data, such as outcome measures, are 100% double entered into the trial database. Extensive range and consistency checks are further enhance the quality of the data.

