#### Trial Management

The trial office is associated with the Edinburgh Clinical Trials Unit in the University of Edinburgh and gives day to day support to the clinical centres. Trial office staff are responsible for all aspects of trial management. These responsibilities include providing research advice and support to all centres, ensuring the timely completion of CRFs in collaboration with all centres, data checking and analysis. The trial office staff are also be responsible for the production of progress reports for the data and safety monitoring committee (DSMC), trial steering committee (TSC), ethics committees and the European Society of Intensive Care Medicine (ESICM) who are funding the study. Publication and dissemination of the study results will be coordinated by the Edinburgh Clinical Trials Unit in collaboration with the Chief Investigator and Principle Investigators.

A senior Trial Manager oversees the study and is accountable to the Chief Investigator. Two Trial Managers supervise the day to day conduct of the trial, including: initiation of trial centres, ensuring training records are maintained and updated, supervision and support of all trial staff, site visits to all participating centres, regularly liaising with all trial investigators, monitoring of centres and site closures. The Secretary/Data Clerk is responsible for all administrative responsibilities of the trial, including: manual data entering from paper CRFs, monitoring response to follow up questionnaires, following up missing data queries and non responses to questionnaires with the local investigators.

The statistical and scientific integrity of a major clinical trial is enhanced by incorporating three distinct statistician roles: the Study Statistician who undertakes all statistical tasks including formal analysis and reporting of data, the DSMC and an Independent Statistician. This Statistician is truly independent having no trial involvement except producing unblinded interim reports for the DSMC at specified time periods.

Subject to additional funding being obtained, a health economist is responsible for the development of the data collection forms required for the economic evaluation, the analysis of economic data and the preparation of the economic evaluation component of the final report.

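### Posting the GOSE does not secure blind assessment of the primary outcome: the ward route uses unblinded local staff, and respondents are not shown to be masked

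*Protocol article*

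**What the plan says.** Treatment Allocation in the protocol article makes two statements in succession. The first is that local staff know the arm: "It is not possible to blind local investigators to allocation as it is obvious clinically which patients are receiving hypothermia". The second is that this does not reach the outcome: "Blinding of outcome data assessment is however be ensured as the GOSE questionnaire is posted to participants by the coordinating centre".

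Follow-up Data then describes how the 6-month GOSE, the sole primary endpoint, is obtained:

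- **Still in hospital at 6 months:** "the research nurse or investigator may visit the patient on the ward to go through the questionnaire with them if this is appropriate".
- **Discharged:** the form goes by post from the coordinating centre. The article expects help to be needed: "It is likely that the patient is unable to complete the questionnaire by themselves due to the nature of their injury". For that reason "a letter will also be sent to the person who gave consent for the patient inviting them to help the patient to complete the form".
- **No reply within 3 weeks:** the shorter GOS is posted.
- **Still no reply, after discharge:** the patient is telephoned. If the patient lacked capacity at discharge and cannot be reached, the consenting person is asked the GOS by telephone. If the patient regained capacity, consented to follow-up and cannot be reached, contact stops.

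The article does not say that relatives or patients are kept unaware of allocation, or that the ward visitor or the telephone caller must be.

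**The concern.** The article gives one reason for calling the assessment blind, namely that the form is posted. Posting determines who delivers the form. It does not change what the person answering it knows, and on the ward nothing need be posted at all. One of the article's own routes therefore lets staff it describes as unblindable take the primary outcome, and another relies on a person who has probably seen whether the patient was cooled.

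The GOSE requires judgement from the respondent or rater, treatment is open, and the design targets an absolute difference of only 7 points. A modest arm-dependent tendency in rating would therefore not be negligible. A trial report that repeated the present sentence would also claim more protection than the procedure gives. Unless respondent and route are recorded, the affected ratings could not be identified afterwards.

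**Working it through.** **1. Claim against procedure**

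| Route (Follow-up Data) | Who rates or answers | Does posting protect it? |
|---|---|---|
| Ward visit | Local research nurse or investigator with the patient | No; local investigators are stated to be unblinded |
| Posted GOSE or GOS | Patient, often with the consenting person | Keeps local staff out; does not mask the respondent |
| Telephone | Patient, or the consenting person for the GOS | Keeps local staff out if the trial team calls; masking of caller and respondent not stated |

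That the consenting person knows the arm is an inference. It rests on three points: cooling is described as clinically obvious, no masking of relatives is described, and the Premature Withdrawal section lets the legal representative withdraw the patient from the intervention alone, which has little meaning without knowing what is being given.

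**2. The plan's own figure**

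Inputs (Sample Size Calculation): 60% versus 53% poor outcome, two-sided 5%, 80% power.

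- Uncorrected: n = [1.96·√(2 × 0.565 × 0.435) + 0.8416·√(0.60 × 0.40 + 0.53 × 0.47)]² / 0.07² = 787 per group, rounded up.
- With continuity correction: 815 per group, as stated.
- Power at 900 per group is 85.0% uncorrected and 83.9% corrected, against a stated 83%.

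The sample size reproduces, and this point does not alter it.

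**3. How much a rating shift could matter (illustration)**

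The article gives neither the share of outcomes rated with knowledge of the arm nor any misclassification rate, so both are assumed. Let f be the share of one arm's outcomes rated with that knowledge, and m the net shift across the poor/good cut among them, with no shift in the other arm. Then:

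- Bias b = f × m.
- SE = √(2 × 0.6 × 0.4 / 900) = 0.0231, or 2.3 points.
- Type I error = Φ(−1.96 + b/SE) + Φ(−1.96 − b/SE).

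| f | m | b (points) | b as share of the 7-point target | Type I error |
|---|---|---|---|---|
| none | none | 0 | 0% | 5% |
| 10% | 5% | 0.5 | 7% | 5.5% |
| 10% | 10% | 1 | 14% | 7.2% |
| 20% | 10% | 2 | 29% | 13.9% |

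The shift is assumed to run in one direction. The Proposed Primary Analysis section plans an ordinal analysis, so these figures are a dichotomised stand-in.

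**The case against.** The strongest reply is that the main route is sound. Discharged patients receive a form from the coordinating centre, and local staff appear only for those still in hospital, only as an option and only where appropriate. This stands. The ward route is a conditional exception, probably for a minority, and the fault lies in an unqualified assurance and a missing safeguard.

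A second reply is that the article claims blinding of assessment, not of respondents, and that respondent awareness is inherent in an open trial with a questionnaire endpoint. This stands in part. It cannot be removed entirely, but it can be stated, and on a form completed by patient or relative the respondent supplies the information being assessed.

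Third, the bias figures depend on chosen inputs. That is correct. In addition, deaths cannot be re-rated and vital status is checked with the family doctor, which limits how many outcomes could move. Patients still on the ward may mostly lie on the poor side of any cut, although an ordinal analysis would also register movement among the lower categories.

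Two stronger readings are tempting. Under Trial Management, the data clerk enters paper CRFs and is responsible for "following up missing data queries and non responses to questionnaires with the local investigators", from which a reader might infer that the clerk is an unblinded assessor. The text does not say that the clerk rates the GOSE, makes the calls or obtains GOSE content from investigators, and the chasing may concern contact details only. A reader might also infer that blinded assessment did not take place at all. An optional route for some patients does not support that.

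**Conclusion.** The point holds in limited form. The article asserts that blind outcome assessment is secured by posting, and its own follow-up procedure does not deliver that for patients assessed on the ward, nor for what respondents know. The conflict over local staff is explicit in the text. Relatives' knowledge of the arm is a strong inference, not a stated fact.

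The share of outcomes affected and the size and direction of any bias are unknown from the document. The illustrated type I error of 5.5% to 13.9% shows only what net shifts of 0.5 to 2 points would do under the assumptions above, and is not an estimate for this trial.

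This should be fixed: the claim is wrong as written and cheap to correct, but the main follow-up route is not undermined. The full protocol or the SAP may contain further safeguards. They would not make the stated reason sufficient while the ward route remains as described.

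**What to change.** 1. **Follow-up Data:** have patients still in hospital at 6 months assessed through the coordinating centre's existing telephone route, by trial-office staff who do not see allocation. At minimum, use someone unaware of the arm. Keep the existing consent limits on contacting relatives.
2. **Scoring:** assign the GOSE category centrally, without sight of allocation.
3. **Data and analysis:** record respondent and route for each form, and specify in the SAP a sensitivity analysis excluding ratings obtained by unblinded staff. Those excluded would be patients still in hospital, a group defined after randomisation, so the result supports the primary analysis and does not replace it.
4. **Treatment Allocation:** once steps 1 and 2 are adopted, replace the assurance with a statement of which parties are blinded, and say that patients and relatives are not masked.

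Six-month mortality is already a listed endpoint and can be read beside the GOSE as an outcome not open to rating bias.

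The cost is a small reallocation of calls among existing staff, one or two CRF fields and a less favourable blinding statement. Respondent awareness remains, but it is declared.

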#### Premature Withdrawal

Participation in any research trial is voluntary and therefore the participant or their legal representative may wish to withdraw from the trial at any point. If this is the case, it should be made clear on a Premature Withdrawal Form whether any previously collected data may still be used for the analysis and which part of the trial the patient is being withdrawn from:

1)Withdraw entirely - the hypothermia intervention is safely terminated, no further data is collected and previous data collected will not be used in the analysis.

2)Withdraw entirely - no further data is collected and the intervention is safely terminated but data previously collected may be used in the analysis.

3)Withdraw from the intervention but be willing to be followed up.

4)Withdraw from being followed up only.

If the patient wishes to withdraw from the trial or their legal representative wishes to withdraw them, they are free to do so without giving a reason and without the patient's medical care or legal rights being affected [47]. If however the patient is withdrawn from the study by the doctor in charge of their care on medical grounds, the reason for this withdrawal must be clearly documented in the data collection form and a serious adverse event form completed if appropriate.

### Data Collection and Checking

Daily data collection starts on the day of randomisation (baseline) for all patients and continues until the ICP monitor has been removed. Data is collected using an electronic CRF. This includes the Modified Oxford Handicap Scale which is completed at hospital discharge. Paper copies of all CRFs are available to centres with little or no access to the internet. All CRFs must be completed in English and is managed by Lincoln, Paris. Blinded and patient identifiable data are stored separately in secure databases. All patient identifiable data are stored by the coordinating centre.

#### Follow-up Data

The patient's General Practitioner/Family Doctor is sent a letter by post to inform them of the patient's involvement in the Eurotherm3235Trial.

Patient outcome is assessed 6 months after injury using the GOSE questionnaire. As this is the primary endpoint of the study, it is vital that this information is obtained. If the patient is still in hospital 6 months after the injury, the research nurse or investigator may visit the patient on the ward to go through the questionnaire with them if this is appropriate. If however the patient has been discharged from hospital, the questionnaire is sent to their residing address. A member of the trial team will telephone the patient's family doctor to find out their vital status before any questionnaires are sent to the patient.

It is likely that the patient is unable to complete the questionnaire by themselves due to the nature of their injury. Therefore a letter will also be sent to the person who gave consent for the patient inviting them to help the patient to complete the form and remind them of the study. This is sent at the same time as the GOSE questionnaire is sent to the patient. If a response is not received from the patient within 3 weeks, they are sent the shorter GOS questionnaire with a covering letter.

If there is still no response, and the patient has been discharged from hospital, an attempt will be made to contact them directly by telephone. If the patient lacked capacity at hospital discharge and cannot be contacted directly by telephone, the person who consented for the patient to be enrolled in the study is telephoned and asked to complete the shorter GOS questionnaire over the telephone.

If however the patient regained capacity before hospital discharge and has given consent to continue to be involved in the follow-up phase of the study, yet cannot be contacted directly by telephone, no further contact is made. This process is discussed during the consent procedure.

Staff in Edinburgh work closely with local investigators to obtain data that are as complete and accurate as possible. Key data, such as outcome measures, are 100% double entered into the trial database. Extensive range and consistency checks are further enhance the quality of the data.

### Statistics and Data Analysis

#### Sample Size Calculation

The primary endpoint for this trial is outcome at 6 months measured by the GOSE questionnaire. The main evidence on therapeutic hypothermia has been gathered by six meta-analyses published between the years 2000 and 2008. These included varying numbers of clinical trials and examined each trial based on an assessment of the quality of randomisation and blinding procedures. All meta-analyses found a trend to positive effects of hypothermia on neurological outcome, but statistical significance was reached in only two [37,38].

A major reason for the failure of previous Phase III trials in TBI has been that they have typically been powered to detect an absolute decrease in poor outcome of around 10%. This is an unrealistic target in view of the enormous heterogeneity of the TBI population. A more modest 7% absolute decrease remains clinically relevant and is more realistic as a hypothesised treatment effect (corresponding to an odds ratio of 0.75). Two groups of 815 give 80% power at the 5% significance level (2-sided) to detect a decrease in poor outcome from 60% to 53% and two groups of 900 would give 83% power to detect the same difference at the same significance level. We aim to enrol 1800 patients in the main trial to allow for loss to follow up. Importantly, we have been conservative with the power calculation to reduce the chance of conducting another underpowered trial in this field.

#### Proposed Primary Analysis

A detailed Statistical Analysis Plan (SAP) setting out full details of the proposed analyses will be finalised before the trial database is locked for analysis. The primary analysis will follow these principles:

• The analysis will be undertaken on the 'intention-to-treat' principle.

• The estimated treatment effect will be presented along with its corresponding 95% confidence interval.

• The analysis of the primary outcome measure, the 6 month GOSE, will exploit the ordinal nature of the outcome scale. It is currently an active research question in both TBI and stroke trial methodology which approach to use to analyse such ordinal outcome scales, the two main options being 'shift analysis' and the 'sliding dichotomy'. The preferred approach will be declared in the SAP, taking into account the results of current on-going methodological research.

• The primary analysis will be adjusted for key baseline covariates, to be specified in the SAP. The unadjusted analysis will also be presented as a sensitivity analysis.

• All interim efficacy analyses reviewed by the independent Data and Safety Monitoring Committee will be interpreted according to the strict Peto-Haybittle guideline so that no adjustment is required to the final p-value to allow for the multiple testing.

#### Other Planned Analyses

*A priori *sub-group analysis will be presented testing the relationship between minimisation factors including: age <45 years, admission post resuscitation Glasgow Coma Score motor response <2, time from injury <12 hours and outcome. The analysis will test for interaction effects, and stricter levels of statistical significance (p < 0.01) will be sought, reflecting the exploratory nature of these subgroup analyses. Only the primary outcome measure will be used in these analyses.

Other exploratory and observational studies will be conducted by some centres. These sub-studies will be run by local Investigators and will require approval by the trial management and steering committees together with further ethical approval. All sub-studies must also have secured external funding.

#### Economic Analysis

The undertaking of economic data collection and analysis will be dependent on obtaining external funding. Details of this analysis will be added when external funding is obtained.

### Adverse Events

The ***only ***serious adverse events to be collected are:

• Bleeding - defined as a new haemorrhage requiring ≥2 units of packed red cells.

• Cardiovascular instability - defined as a systolic blood pressure <90 mmHg for ≥30 minutes [37]. Terminal hypotension is not be collected.

• Thermal burns >5% of body surface area using the Lund-Browder Chart.

• CPP < 50 mmHg for ≥15 minutes.

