Hypotension (lasting >2 hours) and hypovolaemia occurred three times more frequently in the hypothermia group. Bradycardia associated with hypotension also occurred four times more frequently in this group, electrolyte disorders and hyperglycaemia were also found more frequently in the hypothermia group [9]. All of these complications are known side effects of hypothermia. Most are easily preventable with good intensive care and should not be regarded as inevitable consequences of hypothermia treatment. Since even very brief episodes of hypotension or hypovolaemia can adversely affect outcome in TBI, these and other issues may have significantly affected the results of this trial [29-31]. One possible problem was that some of the participating centres had little or no previous experience in using hypothermia. Large centres, familiar with cooling, showed apparently favourable neurological outcomes whereas smaller centres showed poor outcomes.

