### Rationale for Study

The evidence from previous research shows that treatment with therapeutic hypothermia to reduce intracranial hypertension may improve patient outcome after TBI. A recent meta-analysis has shown key relationships between the duration of hypothermia treatment and speed of re-warming with patient outcome [42]. Improved patient outcome was found when hypothermia was continued for between 48 hours and 5 days and patients were re-warmed slowly (1°C/4 hours). Experience with cooling also appears to be important if complications which may outweigh the benefits of hypothermia are to be avoided.

The Eurotherm3235Trial is examining the relationship between therapeutic hypothermia for ICP reduction after TBI and patient outcome. The trial is enrolling patients with TBI who have ICP >20 mmHg that is resistant to stage 1 therapy (Figure 1).

The Brain Trauma Foundation's recommended threshold for treatment of ICP is 20 mmHg [37,43]. Although early cooling after injury is considered to be beneficial, this is offset by failure to show benefit from hypothermia in the absence of raised ICP. Enrolment to the trial is therefore allowed for up to 72 hours following injury. This potential delay in cooling is compensated for, to an extent, by inducing hypothermia with 20-30 ml/kg of refrigerated 0.9% saline given intravenously over 20-30 minutes. No maximum duration of cooling is specified and hypothermia can continue until ICP is no longer dependent on temperature reduction to remain below 20 mmHg. Patients are then slowly re-warmed at a rate of 0.25°C per hour (1°C/4 hours).

The Extended Glasgow Outcome Scale (GOSE) is used to assess patient outcome at 6 months. Many patients with severe TBI are expected to have poor outcome. This outcome questionnaire is used as it is more sensitive to differences between poorer outcome categories after TBI than the 5-point Glasgow Outcome Score (GOS) [44,45].

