#### Other

• 6 month mortality rate

• ICP control

• Incidence of pneumonia across both groups

• Length of stay in the ICU and hospital

• Modified Oxford Handicap Scale score at one month, discharge from the randomising hospital or death, whichever occurs first

• Correlation between the predicted outcome using the modified Oxford handicap scale at hospital discharge and the GOSE Score at 6 months post injury

• Health economics (dependent on additional external funding).

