## Methods/design

This is a pragmatic, multi-centre randomised controlled trial to examine the effects of hypothermia (32-35°C) on outcome after traumatic brain injury. The study is recruiting for 41 months. Participants are randomised to either the control or intervention group (Figure 2). Participants allocated to the control group receive standard care without therapeutic hypothermia. Participants randomised to the intervention group receive standard care with therapeutic hypothermia. Hypothermia is initiated with 20-30 ml/kg refrigerated 0.9% saline given intravenously and maintained using the cooling technique available at that centre. A flowchart has been designed for the induction and maintenance of therapeutic hypothermia in the intervention group. The depth of hypothermia (range: 32-35°C) is guided by ICP with a higher pressure level warranting a cooler target temperature. A guideline has been produced for the detection and treatment of shivering in the intervention group. This has been designed specifically for this trial drawing on:

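### Serious adverse event collection is closed at four defined events, with no category for any other serious harm related to cooling

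*Protocol article*

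**What the plan says.** The Adverse Events section of the protocol article gives a closed list. The emphasis on *only* is the authors' own, and the "serious adverse events to be collected are":

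- a new haemorrhage needing at least 2 units of packed red cells;
- systolic blood pressure below 90 mmHg for at least 30 minutes, terminal hypotension excepted;
- thermal burns above 5% of body surface area;
- cerebral perfusion pressure (CPP) below 50 mmHg for at least 15 minutes.

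The only other mention of an SAE form is under Premature Withdrawal. If the doctor in charge withdraws a patient on medical grounds, the article asks for two things: "the reason for this withdrawal must be clearly documented in the data collection form and a serious adverse event form completed if appropriate".

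Under Review of Clinical Evidence the article describes the harms seen in an earlier large multi-centre trial: "Hypotension (lasting >2 hours) and hypovolaemia occurred three times more frequently in the hypothermia group". It continues: "Bradycardia associated with hypotension also occurred four times more frequently in this group, electrolyte disorders and hyperglycaemia were also found more frequently". It then states: "All of these complications are known side effects of hypothermia".

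In the present trial, hypothermia is started with cold intravenous saline and "maintained using the cooling technique available at that centre" (Methods/design).

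**The concern.** A closed list works only if every serious harm worth knowing about was foreseen and falls inside a definition. Here the list omits harms that the article itself attributes to cooling. It also leaves no place for one that nobody foresaw. Cooling methods differ by centre and at least 70 hospitals are planned, yet the only injury on the list specific to temperature devices is an extensive burn.

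What is at stake is patient safety and the information that reaches the Data and Safety Monitoring Committee (DSMC). That committee oversees participants' safety and may report that treatment is contraindicated. For an unlisted related harm that does not lead to medical withdrawal, it must rely on other forms happening to record the event and on knowing to ask for it.

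**Working it through.** The article gives no figure to reproduce on this point. The check sets the complications named under Review of Clinical Evidence against the four SAE definitions, and then looks for another reporting route.

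**1. Named complications against the list**

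| Complication more frequent with hypothermia | Collected as an SAE? |
|---|---|
| Hypotension | Yes, if systolic pressure is below 90 mmHg for ≥30 min |
| Hypovolaemia | Only if the systolic or CPP threshold is crossed for the stated time |
| Bradycardia with hypotension | Only if the systolic or CPP threshold is crossed for the stated time |
| Electrolyte disorders | No, however serious |
| Hyperglycaemia | No, however serious |

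Count: 1 direct + 2 indirect + 2 unmatched = 5.

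Two further examples fall outside the list. One is a treated bradycardia whose hypotension is corrected within 30 minutes and which causes no qualifying fall in CPP. The other is a complication of the centre's cooling technique that is not a burn and does not cause qualifying bleeding or low pressure.

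**2. Other routes in the article**

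- *Premature Withdrawal.* The SAE form applies when the doctor withdraws the patient on medical grounds, and then at discretion. It does not reach patients who have the harm and stay in the trial. It also sits awkwardly with *only*, since a site cannot tell whether an unlisted event qualifies.
- *Data Collection and Checking.* Daily data run from randomisation until the ICP monitor is removed. The content of the form is not shown, and later events fall outside it.
- *Study Endpoints, Other.* Six-month mortality and "Incidence of pneumonia across both groups" are collected. Neither identifies other non-fatal harms or their relation to treatment.
- *Data and Safety Monitoring Committee.* The committee may request further analyses, but only of data that exist.

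None of these is an open route for reporting a serious related event.

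**3. Illustration of scale (assumed rates)**

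The article gives no rate for unlisted serious harms, so the rates below are assumptions. With n = 900 patients allocated to hypothermia (Sample Size) and a true rate p, the expected number of cases is n × p, and the chance of at least one is 1 − (1 − p)^n.

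| Assumed p | Expected cases, 900 × p | Chance of at least one |
|---|---|---|
| 0.1% | 0.9 | 1 − 0.999^900 = 59% |
| 0.5% | 4.5 | 1 − 0.995^900 = 99% |
| 1% | 9.0 | 1 − 0.99^900 > 99.9% |

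Under the stated rule none of these cases would be collected as an SAE, except possibly through medical withdrawal. The table shows that even an uncommon harm would probably occur in a trial of this size. It does not show that such a harm exists.

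**The case against.** The strongest reply is that the short list is deliberate and sensible. The patients are sedated and ventilated with raised ICP, and a 60% rate of poor outcome is assumed. Serious events are frequent in such a group, and collecting all of them would bury any signal. The list targets the pathway that the article stresses, low blood pressure and low cerebral perfusion, and through it can reach three of the five named complications. The article also regards most of these complications as easily prevented by good intensive care. A harm serious enough to change outcome would contribute to the six-month GOSE, mortality or length of stay in both arms. The daily form may well record electrolytes and glucose.

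Much of this stands. A targeted list is defensible, and the contents of the daily form are unknown. The five-way count concerns known harms, so it says nothing about how often an unforeseen one would arise. The remark under Rationale for Study that experience with cooling matters if "complications which may outweigh the benefits of hypothermia are to be avoided" is about centres' skill, not about event reporting. It shows only that the authors take such harms seriously.

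The reply does not justify closing the list completely. The case for brevity is an argument against collecting every expected intensive care event. It is not an argument against one category limited to serious events judged related to treatment. Outcome comparisons would not identify the cause of a harm. Nor can the gap be put down to condensing a protocol into an article, because the word *only* states the rule outright.

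**Conclusion.** The concern holds. As the article states the rule, a serious related or unexpected harm outside the four definitions is not collected as an SAE, apart from the discretionary form on medical withdrawal. Two of the five complication types that the article itself links to hypothermia match no definition, and two more are caught only through a pressure threshold.

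The number of harms missed cannot be sized. The article gives no rates, and whether the daily form would record such events is unknown. Sample size, power and the primary analysis are untouched. This is a safety-reporting weakness that should be corrected because the correction is cheap, and it does not threaten the validity of the trial.

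**What to change.** Keep the four events as defined and add a fifth item to the SAE form: *any other serious event that the investigator judges related to trial treatment or the cooling device*. Report it to the DSMC by arm, with a short description of each case. Limiting it to related events keeps expected intensive care events out.

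The cost is one form item and slightly more reporting, with no new procedures. The limitation is bias. Local investigators know the allocation, and controls receive no therapeutic hypothermia, so reports will come mostly from the hypothermia arm. The protocol should therefore say that this category is a safety signal and will not be used for a formal comparison between arms.
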